### 2.11. Limitations

The main limitation of this study is non-randomness. Randomness is not possible, due to the ethical reasons described above, and because the parents have the freedom and the right to choose the paediatrician that will care for the child. However, this is compensated for by the fact that it is a homogeneous population for the control and the intervention group, which will reduce the risk of bias.

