## 1. Introduction

Obesity is a global public health problem, and it has been declared the epidemic of the 21st century by the World Health Assembly [1] because of its high prevalence and its association with other chronic diseases [2,3]. The development of preventive strategies must be a priority goal of public health in order to decrease the social and economic burden of obesity [4].

The situation is even more concerning among children, due to its high incidence in developed countries, the appearance of excess weight at younger ages [5,6] and the fast increase in the prevalence of childhood obesity in emerging countries [7].

Childhood obesity is recognized as a disease by the World Health Organization. It is also associated with other pathologies and can lead to psychological damage [8]. The high prevalence of obesity in childhood and adolescence becomes a problem for the health system, since a large proportion of overweight children will be obese in their adulthood [9].

In addition, inequalities in obesity have risen, with greater increases in the prevalence of obesity in the most disadvantaged social groups [10], so that obesity is a marker of social inequalities in health [11].

In Spain, the latest data in school children [12] show a high prevalence of excess weight, with a significant reduction in overweight, but not in obesity [13]. In order to fight against diseases whose causes are related to exposure to social and environmental factors, such as obesity, preventive measures provide the best results. In recent years, programs to prevent childhood obesity have been developed [14,15,16]. However, the effects of these programs on the child population have been scarced in scope [12]. In this sense, in order to confront these results, some authors propose a change in the approach of strategies to prevent childhood obesity [17,18].

Recent knowledge about early programming offers the opportunity to develop new prevention strategies. The concept of early programming has been incorporated into the prevention recommendations for childhood obesity [19,20]. These new strategies should be focused on the maximum-plasticity period of early programming, before and during pregnancy and in the first 2–3 years of postnatal life. This period is critical both for development and for the prevention of childhood obesity.

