The project’s global hypothesis is that an intervention in the first 1000 days of life on the early programming factors related to childhood obesity will achieve more adequate early programming and will decrease the prevalence of childhood obesity. The risk of developing obesity in childhood will be lower when the number of factors accumulated in the individual in this critical first phase is decreased. This improvement in early metabolic programming will be reflected in a lower percent of body fat mass at 2 years of age, compared to the control group.

The aim of the project is to evaluate the effectiveness of a combined multifactorial educational and care intervention for preventing obesity and overweight in childhood, based on the concept of early programming, and developed during pregnancy and the first 2 years of life (the first 1000 days) by a multidisciplinary group in primary care. The specific objectives are:

To analyse the body fat mass at 2 years of age in a control group of children who reach this age between November 2017 and June 2019, belonging to two pediatric quotas of the Basic Health Zone (BHZ) of Puerto Real.

To analyse the body fat mass at 2 years of age in the intervention group of children, whose pregnancies begin between January and December 2018, belonging to four pediatric quotas of the BHZ of Puerto Real. 

To compare the body fat mass at 2 years of age between the control and intervention groups.

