## 2. Materials and Methods 

### 2.1. Study Design

This study is a quasi-experimental design with two groups (control and experimental group), in which the results on body fat in 2-year-old children, obtained after a combined educational and care intervention, are compared with those obtained after the usual intervention developed in our Clinical Management Unit (CMU). 

Randomization could not be carried out for ethical reasons; once the intervention has begun, we should not deprive a part of the population of it. Similarly, as it is a small town, there could be contamination between groups (transfer of information). Therefore, a historical control group of the same population consisting of children who turn 2 years old during 2018 will be used.

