### 2.2. Study Population

The target population is two-year-old infants. The BHZ of Puerto Real (Cádiz) is constituted by two CMUs: Puerto Real, with four pediatric quotas and Casines, with two. The project will be developed in the CMU Puerto Real. There are no significant sociocultural differences between the different quotas. Since the number of births in the BHZ during the previous year was 320, it is expected that, on average, 50 newborns will be added annually to each quota. 

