### 2.4. Recruitment

A single midwife will take charge of maternal education in the CMU Puerto Real, which includes the Ribera del Muelle Health Centre where there are three paediatricians, and the Rio San Pedro Health Centre where there is one. Therefore, all pregnant women will receive exactly the same information about the intervention. After birth, the parents will decide in which of the six paediatricians of the BHZ of Puerto Real they will register their children, and we cannot interfere in that decision.

The study population of the control group will be constituted by two-year-old children of two quotas of the Basic Health Zone of Puerto Real. The paediatricians have employment stability for at least the expected duration of the study and have agreed to participate. The inclusion in the study and the data collection will be carried out in the health controls at 2 years of age at the same time as the intervention in pregnant women begins, so that neither mothers during pregnancy nor infants after delivery will have been influenced by the intervention. Once the intervention ends, their results will be analyzed from the data obtained from the mother–child pairs.

Following the above criteria, all newborns assigned to the four pediatricians of the unit that meet the inclusion criteria will be included in the intervention group. Two paediatricians from the same unit will also participate in the data collection for the control group. Including a greater number of pediatricians is necessary to obtain the calculated sample of the intervention group, due to the decrease in the birth rate observed in recent years. Inclusion in the study will be done at the first pediatric visit of the newborn.

The inclusion criteria are: two-year-old infants whose pregnancy begins in the 14 months following the start of the intervention, and whose mothers have made the complete follow-up of their pregnancy in the Care Process of Pregnancy Childbirth and Puerperium and begun the monitoring of child health controls of the Andalusian Children and Adolescents Health Program in our unit. The exclusion criteria are: infants whose parents do not authorize their participation in the study in writing.

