### 2.8. Measures and Outcomes

#### 2.8.1. Independent Variables 

Weight gain during pregnancy. The difference in maternal weight between the first visit (weeks 4–7) and the last one (week 38) is calculated. If the weight on the last visit is not registered, it is calculated with the final pregnancy weight recorded in the hospital discharge report. It will be classified as adequate or excessive according to the accepted values of weight increase by the pre-gestational body mass index (BMI) of the Institute of Medicine (IOM) and National Research Council [61].Mother’s body mass index (BMI) at the first visit (weeks 4−7). This will be evaluated as a continuous measure.Maternal nutritional status. Classified as obesity, overweight, normal weight or low weight.Maternal smoking during pregnancy. Active smoker, passive smoker and non-smoker. The mother is considered an active smoker if she consumes any amount of tobacco.Gestational diabetes.Caesarean section.Newborn sex.Newborn weight. Registered in hospital visit (newborn measures).Duration of exclusive breastfeeding. Full months of exclusive breastfeeding are considered.Weight gain in the first four months. The difference in the infant’s weight between birth weight and fourth-month-postnatal weight at the visit is calculated as grams/day. As secondary outcomes, weight gain in the first six months and in the first year are also calculated.Introduction of complementary food, before or after 4 months of age.Vitamin D supplementation (400 IU/day) in the first year. Full months of supplementation are considered.Type of milk in second year. Classified according to the type of milk that was consumed the largest number of months: breastfeeding, growing milk or cow milk.BMI at 1 year of life.

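### Section 2.11 says a homogeneous population makes up for non-randomisation, but the two groups reach age 2 in separate calendar periods and the listed variables allow only a partial check of homogeneity

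*Protocol article*

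**What the plan says.** Section 2.11 of the protocol article names the lack of randomisation as the main limitation. It then states that "this is compensated for by the fact that it is a homogeneous population for the control and the intervention group", and adds that this lowers the risk of bias. It does not mention calendar time.

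The only support for homogeneity is one sentence in Section 2.2, given without data: "There are no significant sociocultural differences between the different quotas".

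The article gives more than one version of the windows:

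- **Controls:** the objectives in Section 1 take "children who reach this age between November 2017 and June 2019". Section 2.1 instead says "a historical control group of the same population consisting of children who turn 2 years old during 2018 will be used".
- **Intervention group:** the objectives take children "whose pregnancies begin between January and December 2018". Section 2.4 has infants "whose pregnancy begins in the 14 months following the start of the intervention". Section 2.7 places first pregnancy visits between January 2018 and February 2019, at weeks 4 to 7.

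Section 2.8.1 lists the independent variables, and Section 2.10 models the outcomes on them with a generalized linear model. The introduction treats obesity as socially patterned, with "greater increases in the prevalence of obesity in the most disadvantaged social groups".

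**The concern.** Homogeneity across quotas within one health zone is a statement about place. The threat in a historical-control design is time: secular change in body composition, changes in usual care, drift in measurement, and change in which families take part. If every control is measured before every intervention child, no covariate adjustment can separate the intervention from the period.

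The groups also differ in how they are formed. Controls come from two quotas, enter at the 2-year visit and need do nothing more (Sections 2.4 and 2.6). Intervention children come from four quotas, enter soon after birth and must attend until age 2. Selection through attrition can therefore act on one group only.

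The article itself points to social position as a determinant of obesity, yet lists no variable that measures it. A shift in family mix could be reported as an intervention effect, or could hide a real one. The article hopes to see the intervention made routine in primary care, so how firmly the result can be interpreted matters.

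**Working it through.** **1. Do the age-2 windows overlap?** Inputs are the windows above. Assumptions: 280 days from the start of pregnancy to birth, plus 2 years. For the first-visit version, 4 to 7 weeks (28 to 49 days) are subtracted from the 280 days.

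Intervention children then turn 2 as follows:

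- pregnancies starting January to December 2018: 7 Oct 2020 to 7 Oct 2021
- pregnancies starting within 14 months from January 2018: 7 Oct 2020 to 5 Dec 2021
- first visits January 2018 to February 2019: 19 Aug 2020 to 7 Nov 2021

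| Control window | Intervention version | Empty gap (months) | Midpoint gap (years) |
|---|---|---|---|
| Nov 2017–Jun 2019 | Jan–Dec 2018 | 15.3 | 2.60 |
| Nov 2017–Jun 2019 | 14 months | 15.3 | 2.68 |
| Nov 2017–Jun 2019 | first visit | 13.7 | 2.58 |
| Calendar 2018 | Jan–Dec 2018 | 21.2 | 2.77 |
| Calendar 2018 | 14 months | 21.2 | 2.85 |
| Calendar 2018 | first visit | 19.6 | 2.74 |

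No combination overlaps.

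**2. What can be checked from the listed variables?** Section 2.8.1 has gestational weight gain, first-visit maternal BMI, maternal nutritional status, smoking in pregnancy, gestational diabetes, caesarean section, newborn sex and weight, feeding, vitamin D, milk type, early weight gain and BMI at 1 year. It has no maternal age, parity, education or other social measure, and no gestational age at birth. Several listed items (gestational weight gain, smoking, breastfeeding, vitamin D, milk type, early weight gain) are things the intervention aims to change, so they are poor adjusters for baseline differences. First-visit maternal BMI is the clearest usable one. Newborn sex would not be expected to differ between cohorts.

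**3. How much could a modest shift matter?** The plan gives no figure on this point. Its only computed design figures, precision of about 9% and 7% (Section 2.5), can be reproduced as 1.96 × 0.5/√m × √((320 − m)/319). With m = 0.85 × 100 = 85 this gives 9.12%, and with m = 0.85 × 150 = 127.5 it gives 6.74%. So the stated figures match a 15% loss in both groups, and I use those numbers as one case.

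Standard error of a mean difference in SD units: √(1/n₁ + 1/n₂).

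- With losses: √(1/85 + 1/127.5) = 0.140
- Without losses: √(1/100 + 1/150) = 0.129

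Rejection rate at two-sided 5% with no true effect and a shift b: Φ(b/SE − 1.96) + Φ(−b/SE − 1.96). The values of b are assumptions; the document gives none.

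| b (SD) | 85 vs 127.5 | 100 vs 150 |
|---|---|---|
| 0.1 | 11% | 12% |
| 0.2 | 30% | 34% |

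The difference detectable with 80% power is (1.96 + 0.84) × SE, which is 0.39 SD with losses and 0.36 SD without. A shift of 0.1 to 0.2 SD is thus 26 to 51% of 0.39 SD, or 28 to 55% of 0.36 SD.

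**The case against.** The design is disclosed: Section 2.1 calls it quasi-experimental with historical controls and gives ethical and contamination reasons. Section 2.11 speaks of reducing bias, so a reader who infers that the authors claim to have removed it goes beyond the text. That stands. What remains is the assertion of compensation and the silence on time.

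A reader might also infer that homogeneity cannot be checked at all. The documents do not support that. First-visit maternal BMI, smoking and newborn sex are listed and a multivariable model is planned, so a partial check is possible.

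The study's data collection sheet (Section 2.9) is not shown and may hold further fields, such as maternal age. This weakens the covariate half of the point, though the article's explicit list, which feeds its model, does not contain them. It does not touch the wording half.

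Measurement drift is limited by named instruments, triplicate skinfolds and one observer per quota (Section 2.9). These do not exclude drift, or a different observer mix between two and four quotas.

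The 0.1 to 0.2 SD shift is assumed, and losses may be fewer among controls, who need no follow-up. Hence both sets of figures are given. Nothing in the document shows that a shift exists or gives its direction, so it would be wrong to conclude that the result will be biased in favour of the intervention.

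**Conclusion.** The point holds in this form. Group and calendar period coincide under every version of the article's dates, with an empty interval of about 14 to 21 months and midpoints about 2.6 to 2.9 years apart. The similarity of quotas asserted in Section 2.2 does not address this, so the compensation claimed in Section 2.11 is not a property of the design. With no socio-economic or parental demographic variable in the list, homogeneity can be only partly shown or adjusted for.

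The non-overlap rests on the article's dates plus a 40-week pregnancy. The error rates of 11 to 30% (15% losses in both groups) or 12 to 34% (no losses) are illustrations that rest on the assumed shifts and a normal approximation. The study can proceed, but the claim and the covariate set should be corrected.

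**What to change.** **(a) Reword Section 2.11.** Replace the compensation clause with a statement that this is a before-after comparison with historical controls, which cannot separate the intervention from period and other cohort differences. Limit the conclusions accordingly. This costs nothing and is needed whatever data are collected.

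**(b) Extend the covariates.** Extract maternal age, parity and gestational age at birth for both groups from the Diraya records already being searched, where they are held there, and maternal education where obtainable. Tabulate them by group. Adjust the group comparison for the pre-exposure maternal variables together with first-visit maternal BMI. Gestational age at birth follows the start of the intervention, so it belongs in the table and not in that adjustment set. The cost is a small extraction burden and possible missing data, especially education for controls already seen. This addresses measured case-mix only and cannot remove the period effect.

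**(c) Optional at most.** A difference-in-differences on routine 2-year BMI from the two Casines quotas over both periods would cover BMI only. It is open to contamination, because mothers taught in the Puerto Real unit may register with any of the six paediatricians. It would also be imprecise. Assuming about 100 Casines children per period (two quotas of about 50), the SE is √(1/85 + 1/127.5 + 1/100 + 1/100) ≈ 0.20 SD, with about 0.56 SD detectable at 80% power. That could not resolve a shift of 0.1 to 0.2 SD.

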## 3. Ethics and Dissemination 

The trial does not involve any risk to participants and their offspring. Children who are not included in the study at birth are not left unprotected, but continue to receive the recommendations and reviews that are currently developed within the A-CAHP. Signed informed consent is obtained from all participants: mothers and parents or legal guardian as representatives of children, both in intervention and control groups (Supplementary A–C). The rights, privacy and integrity of the participants are guaranteed. The investigation will be carried out in accordance with the precautionary principle, to prevent and avoid risks to life and health, observing compliance with the recommendations set forth in the Declaration of Helsinki. There is authorization from the primary care management of the Bahía de Cádiz-La Janda District, and ethical approval was obtained from the Regional Committee of Ethics (Comité Coordinador de Ética de la Investigación Biomédica de Andalucía, CCEIBA) (Supplementary D). 

There is a high percentage of women who begin pregnancy with overweight or obesity. Due to the public health problem posed by obesity in the world and the lack of effectiveness demonstrated by the current interventions, it is necessary to design and implement interventions aimed at the prevention of obesity with a different perspective. This intervention represents a new approach in a key period for the development of obesity, in which few interventions have been developed in this regard. For all this, it is expected that this study will provide evidence on the importance of the prevention of obesity from the critical period of the first thousand days of life, being able to establish as a standard intervention in primary care. Results from this study will be disseminated at international congresses, in regional and national conferences and in peer-reviewed journals. Due to its interdisciplinary nature, this research is of interest for clinicians, researchers and parents.

## 4. Conclusions

Knowledge of the early risk factors related to childhood obesity offers us novel approaches to design prevention strategies. These effective strategies must cover the gestation period, and the first and second year of postnatal life because of the fact that they are considered critical periods for the childhood obesity prevention. Moreover, as many early risk factors as possible, accessibility, cost effectiveness, and sustainability must be taken into account.

The article presented is a novel protocol. The intervention will be integrated into routine primary care health programs and will not require additional effort from professionals or equipment. It could be a new intervention capable of reducing the prevalence of childhood obesity.
